### Strategies to improve adherence to interventions {11c}

All sessions are standardized and matched for duration, using objective HRR and subjective Borg RPE measures of intensity. The exercise physiologist prescribes exercise intensity for each participant based on screening exercise testing. Exercise sessions include up to 3 participants and are supervised by an interventionist. The interventionist assesses participant’s HRs with HR monitor, activity tracking, pulse oximeter, or manual method and measures blood pressure to guide participants for 5-min warm-up, prescribed exercise, and 5-min cool-down (or 10-min cool-down for HIIT). The interventionist assesses and documents participant HRs, RPE, talk test, and over-exertion signs/symptoms every 5 min and blood pressure every 10–15 min. Participants can leave after HR and blood pressure return to pre-exercise levels. The proper use of the RPE is continuously reinforced.

Attendance and session dose achieved are monitored in weekly intervention meetings. Any issues are addressed, and staff re-training are conducted. Based on lessons from our previous trials, we (1) make up any missed regular sessions each week, e.g., the participant completed 2 sessions in a week, and efforts will be made to make up the 3rd session for the week; (2) start to offer the 4th session (makeup session) per week if attendance is < 100%; (3) check each session report weekly and implement strategies to improve adherence to session intensity/duration; and (4) make up for absent weeks.

### Relevant concomitant care permitted or prohibited during the trial {11d}

Concurrent enrollment in another intervention trial is prohibited during the trial.

### Provisions for post-trial care {30}

No provision for ancillary and post-trial care and for compensation to those who suffer harm from trial participation.

### Outcomes {12}

Primary outcomes are aerobic fitness measured at 0, 3, 6, 9, and 12 months and WMHv measured at 0, 6, and 12 months. Secondary outcomes (memory, physical function, BPSD, QoL, caregiver burden) and plasma biomarkers (Aβ_42/40_, p-tau181, t-tau, NfL) are assessed at 0, 3, 6, 9, and 12 months. Exploratory outcomes include discrete cognitive domains (attention, working memory, processing speed, executive function, visuospatial ability, language, other MRI and plasma biomarkers, and study partner outcomes).

#### Primary outcomes

Aerobic fitness is assessed with the peak oxygen consumption (VO_2peak_) from the cycle-ergometer test [24] (primary test) and the maximal walking distance in meters from the SWT [25] (secondary test). The cycle-ergometer test is performed in a post-absorptive state. Participants begin to cycle at a comfortable speed, with the intensity increased every minute by increasing the resistance equivalent to 15–20 W, to reach volitional fatigue or termination criteria per American College of Sports Medicine guidelines: inability to maintain cadence, exhaustion, desire to stop, and clinical indications in 8–12 min [24]. VO_2_, HR, and heart rhythm are continuously monitored via indirect calorimetry and electrocardiogram, and RPE in the last minute of each stage and at peak. VO_2peak_ is defined as the average VO_2_ measured in the final 8 breaths immediately prior to the termination of the test. The SWT stresses participants to peak performance by walking circuits around 2 markers 9 m apart while being paced by a recording. Each minute, pacing increases to promote volitional fatigue. The SWT lasts 5–15 min with a test–retest reliability of 0.76–0.99 [25]. Distance walked on the SWT is used as a measure of aerobic fitness.

WMHv is assessed from MRI FLAIR images using the lesion segmentation toolbox [26]. MRI acquisition: A comprehensive MRI sequence protocol is performed on a Discovery MR 750 3 T MRI system and a 32-channel head coil using ADNI-compatible sequences optimized for our scanner [27, 28]. The MRI protocol includes a sagittal 3D T1-weighted volumetric IR-FSPGR pulse sequence to assess brain structure; a sagittal 3D T2-weighted FLAIR pulse sequence for WMHv and cerebrovascular disease; a T2* heme-weighted GRE sequence for microhemorrhages; an axial 3D pCASL pulse sequence to assess brain perfusion; a diffusion tensor imaging (DTI) pulse sequence for white matter integrity; a field map pulse sequence to correct functional MRI and DTI images for spatial distortions; an echo planer functional MRI sequence as participants rest quietly with their eyes open for resting state brain networks; and an oblique high-resolution volumetric pulse sequence for hippocampal subfields. MRI data are archived using an XNAT system and standard QC/QA procedures are utilized. MRI analysis: MRI will be analyzed using FreeSurfer (v7.1) [29] and semi-automated segmentation algorithms [30].

#### Secondary outcomes

Memory is measured with the AD Uniform Data Set Wechsler Memory Scale-Revised Logical Memory Story A and B Immediate and Delayed Recalls and Craft Story 21 immediate and delayed recall [31]. Physical function is assessed by the FAQ, Short Physical Performance Battery (SPPB) [32], Alzheimer’s Disease Cooperative Study—Activities of Daily Living (ADCS-ADL) [33], Mini Balance Evaluation Systems Test [34], dynamometer, and 6-min walk test (6MWT) [35, 36]. SPPB tests balance, gait speed, and sit to stand (score 0–12, > 0.90 reliability) [21]. ACDS-ADL evaluates the ability to perform ADLs with Cronbach’s alpha 0.64–0.87 and intraclass correlation coefficients 0.62–0.73 [33]. Mini Balance Evaluation Systems Test is a clinical balance assessment tool that shows excellent criterion validity across populations with neurological conditions (*r* = 0.72–0.85) [34]. Muscle strength is measured with Biodex muscle function test (lower extremity strength) and grip strength (upper extremity) dynamometer. 6MWT records peak walking distance in 6 min (0.98-0.99 reliability) [37, 38]. BPSD is measured with the Neuropsychiatric Inventory Questionnaire-Caregiver (NPI-Q) for presence/severity of 12 BPSD in the previous month (score 0–36, 0.91 interscale correlation) [37]. Burden is assessed using the 4-item Zarit Burden Interview (score 0–110 [0.83–0.89 internal consistency] [38]) and NPI-Q. NPI-Q evaluates caregiver distress due to BPSD (score 0–60, 0.92 interscale correlation) [37]. QoL is tested with the 13-item QoL-AD (score 13–52, Cronbach’s *α* 0.84–0.88 [39]).

Plasma biomarkers include Aβ_42/40_, p-tau181, t-tau, and NfL. Standard collection and processing protocols [40–43] are followed to reduce pre-analytical variations that could affect biomarker levels: (i) collect blood samples after at least 8 h of fasting (only water, black coffee, black tea, and medications allowed) and at the same time in the morning (between 8:30 am and 11 am) and (ii) collect blood at least 24 h after the last intervention session. The phlebotomist follows a venous-blood collection protocol and collect a total of 18 mL of blood into 3 6-mL plasma (EDTA-treated) tubes, then store the samples on wet ice until processing. The Clinical Research Services lab technician processes and aliquots the specimens using the established protocol and stores aliquoted samples in a − 80 °C freezer. We will perform biomarker measurements in year 5 to be cost-effective and reduce variability in measurements using the best assays available then and use a rigorous process to authenticate these key biochemical resources.

#### Exploratory variables and covariates

Discrete cognitive domains are assessed with the number span test forward for attention [44], number span test backward for working memory [44], Trail Making Test (TMT) Part A for processing speed [45], TMT Part B for executive function [45], Benson complex figure for visuospatial ability [46], multi-lingual naming test [47], phonemic test F and L (P and M for Spanish speakers), and animals/vegetables list generation for language [48]. MRI and non-AT(N) plasma markers, study partner outcomes, and potential covariates are assessed as detailed in Table 2.

**Table 2 Tab2:** Variables, measures, and data collection timepoints (S: screening; 0: baseline)

Variables	Measures (categorical data; otherwise, continuous data)	S	Month				
			**0**	**3**	**6**	**9**	**12**
**Primary outcomes**							
Aerobic fitness	Peak cycle-ergometer test; shuttle walk test	x		x	x	x	x
WMHv	Magnetic resonance imaging (MRI)	x			x		x
**Secondary outcomes**							
Memory	AD Uniform Data Set Wechsler Memory Scale-Revised Logical Memory Story A and B, Craft Story 21 Recall		x	x	x	x	x
Physical function	Functional Activities Questions*, 6-min walk test, Short Physical Performance Battery, ACDS-ADL**, Mini Balance Evaluation Systems Test, Biodex muscle function test, grip strength		x	x	x	x	x
BPSD	Neuropsychiatric Inventory-Caregiver (NPI-Q)*		x	x	x	x	x
Quality of life	Quality of Life-AD**		x	x	x	x	x
Burden	4-item Zarit Burden Interview***, NPI-Q***		x	x	x	x	x
**Plasma biomarkers**							
Amyloid-beta (Aβ)	Plasma Aβ_42/40_ ratio		x	x	x	x	x
Tau	Plasma phosphorylated tau 181		x	x	x	x	x
Neurodegeneration	Plasma total tau, neurofilament light chain		x	x	x	x	x
**Potential covariates**							
Demographics	Age, education, sexº, race/ethnicityº, family historyº, living arrangementº, occupationº, retirement, family historyº	x					
Severity of cognitive impairment	Montreal Cognitive Assessment	x		x	x	x	x
Depression	Geriatric Depression Scale-15	x		x	x	x	x
Anxiety	Generalized Anxiety Disorder-7	x		x	x	x	x
APOE genotype	Allele combinationsº		x				
Vascular risk	Framingham Vascular Risk Score		x				
Lifestyle	Leisure Time Satisfaction, Physical Activity Scale for the Elderly		x	x	x	x	x
Sleep efficiency	Actigraphy**, Consensus Sleep Diary**		Monthly				
Comorbidity	Charlson Comorbidity Index	x		x	x	x	x
Medications	Numbers of drugs and drug classes	x		x	x	x	x
Condition changes	Medical conditions, medications, events (e.g., falls), health service use		x	x	x	x	x
Fall risk	Timed Up and Go Test, Mini-Best Test, Fall Calendar, Falls Follow-up		x	x	x	x	x
Adherence	Attendance rate, % sessions meeting prescription		x	x	x		
Social interaction	Engagement and Independence in Dementia Questionnaire**		x	x	x	x	x
**Exploratory variables**							
Executive function	Trail Making Test Parts A and B, number span test forward and backward		x	x	x	x	x
Visuospatial ability	Benson complex figure		x	x	x	x	x
Language	Multilingual naming test, phonemic test F and L (P and M for Spanish speakers), animal and vegetables list generation		x	x	x	x	x
Other biomarkers	MRI hippocampal volume, cortical thickness, whole-brain atrophy; emerging blood biomarkers		x		x		x
Study partner outcomes	Dyadic Relationship Scale***, Positive Aspects of Caregiving***, Personal Well-Being Index***, CES-D-10***, Leisure Time Satisfaction Scale***		x	x	x	x	x

Note. Aerobic fitness and WMH volume assessed during screening will be used as 0 month

^*^Completed by study partners on participants

^**^Completed by both participants and study partners on participants

^***^Completed by study partners on selves

measures are completed by participants unless noted with *, **, ***

measures are continuous data unless noted with o that refers to categorical data

### Participant timeline {13}

Participants are recruited through referrals, registries, community events, social media, and newspaper advertisement. Respondents are screened over the phone, in-person, medical clearance, and exercise testing/MRI. The phone screen assesses cognitive symptoms, exercise and MRI contraindications. During in-person interview, informed consent or surrogate consent/assent is obtained, and global cognition is assessed with MoCA. After the in-person interview, medical clearance is obtained from participant’s primary care providers and cardiologist for those with significant cardiac history. Once medical clearance is received, participants undergo the symptom-limited cycle-ergometer exercise test to further rule out unknown heart conditions and prescribe individualized exercise doses. If no abnormality is identified from the exercise test, participants will undergo MRI. Those without MRI abnormality will proceed to baseline data collection of outcomes (Table 2). If any clinically significant abnormality was identified, participants will be referred to their providers for further evaluation and can only re-engage with the trial with medical re-clearance. Afterwards, they will be formally enrolled in the trial and randomized by the study staff designated to perform randomization. Participants will engage in their assigned exercise for 6 months and be followed for another 6 months. Outcomes (Table 2) will be assessed at 3, 6, 9, and 12 months (Fig. 2).

**Fig. 2 Fig2:**
[figure not shown]
Schedule of enrollment, interventions, and assessments

### Sample size {14}

Assuming 18% attrition at 6 months and 25% attrition at 12 months, the sample size of 108 participants should result in a population of *n* = 89 at 6 months and *n* = 81 at 12 months. Under H1a, tests comparing participants assigned to MICT vs. control at R1, 89 complete cases (60 intervention [MICT, MICT + HIIT, MICT + CARE]; 29 control) at 6 months should result in 80% power to detect significant between-group differences in VO_2peak_ and WMHv changes, assuming a standardized between-group difference of *d* = 0.65 (based on a clinically meaningful difference in VO_2peak_ of 3.12 mL/kg/min) and SD = 4.8 (derived from previous research [49]), a pre-post correlation (*r*) in VO_2peak_ of 0.50, and *α* = 0.05 [50]; at 12 months, 81 complete cases (54 intervention; 27 control) should result in 80% power to detect differences of *d* ≥ 0.60, assuming pre-post *r* of 0.50 and *α* = 0.05. For models under H1b, 89 complete cases at 6 months should result in 80% power to detect between-group differences in change of *d* ≥ 0.57 for memory, quality of life (QoL), physical function, and behavioral and psychological symptoms of dementia (BPSD) scores, assuming pre-post *r* of 0.50 and *α* = 0.05; at 6 and 12 months, 81 complete cases should afford power to detect differences in change of *d* ≥ 0.60. For H2a, simulations conducted in R with the latest version at the time of data analyses (20,000 replications for each of 7 effect size scenarios) indicate that tests for a monotonic ordering of group means (i.e., MICT + HIIT > MICT + CARE > MICT > stretching) on VO_2peak_ should have power ≥ 80% for orderings comprising small MICT + HIIT vs. MICT + CARE and MICT + HIIT vs. MICT differences (*d*s = 0.25–0.35) and moderate MICT only vs. stretching differences (*d*s = 0.40–0.55). For H2b, assuming *n* = 13 per group, logistic-regression models are 80% powered to detect large between-group (MICT + HIIT vs. MICT + CARE) differences in number of responders (vs. non-responders), e.g., ≤ 2 non-responders in MICT + HIIT vs. ≥ 11 non-responders in MICT + CARE at *α* = 0.05. For H3, potential mediation of exercise effects (**X**: MICT [*n* = 59] vs. control [*n* = 30]) on memory (**Y**s) through AD/ADRD plasma biomarkers (**M**s) is ≥ 80% powered to detect mediated effects comprising modest direct associations (*r*^2^s ≥ 0.12) between groups (at R1) and each putative mediator (X → M link) and between each mediator and memory (M → Y link) [51].

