**Methods:**

This stage II trial is a Sequential, Multiple Assignment, Randomized Trial (SMART). The hypothesis is that MICT augmented with high-intensity interval training (HIIT) or combined aerobic and resistance exercise (CARE) will improve aerobic fitness, WMHv, and AD/ADRD plasma biomarkers. This trial will enroll 108 dyads (participants and their study partners). Participants (*n* = 108) are randomized using a 2:1 allocation ratio to 3-month MICT or 6-month stretching control. After the initial 3-month intervention period for participants assigned to MICT, aerobic fitness is measured with peak oxygen consumption (VO_2peak_) from a cycle-ergometer exercise testing and the shuttle walk test to identify non-response (< 5% increase). Non-responders are subsequently re-randomized (1:1) to either HIIT or CARE for 3 months. Responders continue MICT. All participants are followed for an additional 6 months post-intervention. Primary outcomes are VO_2peak_ measured at 0, 3, 6, 9, and 12 months and WMHv at 0, 6, and 12 months. Secondary outcomes include memory, physical function, behavioral and psychological symptoms of dementia (BPSD), quality of life (QoL), caregiver burden, and AD plasma biomarkers. This trial has 80% power, assuming 18% and 25% attrition at 6 and 12 months, respectively, to detect changes in aerobic fitness.

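### The H1 power figures mix two methods (80% is attached to both d = 0.65 and d ≥ 0.57 for the same 89 cases), and the 80% claim for co-primary WMHv rests on VO2peak inputs only

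*Protocol article*

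**What the plan says.** All the figures are in Protocol article, Sample size {14}.

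- **H1a, 6 months:** "89 complete cases (60 intervention [MICT, MICT + HIIT, MICT + CARE]; 29 control) at 6 months should result in 80% power". The effect is introduced with "assuming a standardized between-group difference of *d* = 0.65", "based on a clinically meaningful difference in VO_2peak_ of 3.12 mL/kg/min", with an SD of 4.8, "a pre-post correlation (*r*) in VO_2peak_ of 0.50, and *α* = 0.05".
- **H1a, outcomes covered:** the same sentence says that these cases "should result in 80% power to detect significant between-group differences in VO_2peak_ and WMHv changes".
- **H1a, 12 months:** 81 cases (54 and 27) have 80% power for *d* ≥ 0.60, again with *r* = 0.50 and α = 0.05.
- **H1b, 6 months:** "89 complete cases at 6 months should result in 80% power to detect between-group differences in change of" *d* ≥ 0.57, with the same *r* and α.

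Statistical methods {20a} plans a baseline-adjusted, ANCOVA-type linear model for H1a and parallel models for H1b. It also plans Holm and fixed-sequence procedures for multiple tests. Outcomes {12} makes aerobic fitness and WMHv both primary. The power paragraph does not say whether α is one-sided or two-sided.

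**The concern.** With the number of cases, pre-post correlation, α and type of model all fixed, only one standardized difference has 80% power. The paragraph gives two, 0.65 and 0.57, so they cannot both come from one calculation. With sidedness unstated, the reader cannot tell which calculation governs. If it is the one behind 0.65, the H1b and 12-month claims are too high. If it is the one behind 0.57, the headline VO2peak power is understated.

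WMHv is a separate matter. It carries an 80% claim as a co-primary outcome, but the paragraph gives no WMHv difference, SD or correlation. If the WMHv result were null, readers would judge it against a power figure that had no WMHv input.

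**Working it through.** **Inputs (Sample size {14}).** Difference 3.12 mL/kg/min; SD 4.8; *r* = 0.50; α = 0.05; 60 and 29 cases at 6 months; 54 and 27 at 12 months. Sidedness is not given, so both were tried.

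**Figures that reproduce.** 3.12/4.8 = 0.65. 108 × 0.82 = 88.6, or 89. 108 × 0.75 = 81.

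**Formula.** Power comes from the non-central *t* distribution with noncentrality *d* / (*f* × √(1/n₁ + 1/n₂)). The factor *f* scales the SD according to the analysis:

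- change score: *f* = √(2(1 − *r*)) = √(2 × 0.5) = 1, the same as an unadjusted comparison of follow-up values;
- ANCOVA: *f* = √(1 − *r*²) = √0.75 = 0.866.

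The root term is √(1/60 + 1/29) = 0.226 at 6 months and √(1/54 + 1/27) = 0.236 at 12 months. For example, at *d* = 0.65 and 6 months the noncentrality is 0.65/0.226 = 2.87 by change score and 0.65/(0.866 × 0.226) = 3.32 by ANCOVA.

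**Power for the three stated claims**

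| Method | d = 0.65, n = 89 | d = 0.57, n = 89 | d = 0.60, n = 81 |
|---|---|---|---|
| Two-sided change score | 81.1% | 70.3% | 71.0% |
| One-sided change score | 88.6% | 80.4% | 81.0% |
| Two-sided ANCOVA (planned model) | 90.7% | 82.1% | 82.7% |
| One-sided ANCOVA | 95.0% | 89.3% | 89.8% |

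**Detectable d at 80% power**

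| Method | 60/29 | 54/27 |
|---|---|---|
| Two-sided change score | 0.641 | 0.669 |
| One-sided change score | 0.567 | 0.591 |
| Two-sided ANCOVA | 0.555 | 0.579 |

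No row of the first table puts all three claims close to 80%. The 0.65 belongs with a two-sided change-score or unadjusted test. The 0.57 and 0.60 agree with each other: they fit a one-sided change-score test or, slightly conservatively, the planned two-sided ANCOVA. The figure out of line is the 80% attached to 0.65.

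**WMHv.** Of the three inputs to the 80% claim, the difference and the correlation are labelled as VO2peak values, and 4.8 is the divisor that turns the VO2peak difference into 0.65. The document gives no pre-post correlation for WMHv, so the range below is an assumption. By two-sided ANCOVA with 60/29, the detectable difference in baseline SDs is about 0.641 × √(1 − *r*²):

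| Assumed r | Detectable difference, 6 months |
|---|---|
| 0 | 0.641 |
| 0.3 | 0.611 |
| 0.5 | 0.555 |
| 0.7 | 0.458 |
| 0.9 | 0.279 |

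For a true WMHv effect of 0.3 baseline SD (also an assumption), power would be 26% at *r* = 0, 33% at *r* = 0.5 and 85% at *r* = 0.9. The answer turns on quantities that the paragraph does not give.

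**The case against.** The strongest defence is that under the planned two-sided ANCOVA every H1 claim reaches at least 80%. The 0.57 and 0.60 are then slightly cautious (true detectable values 0.555 and 0.579), and the error at 0.65 is on the safe side. This stands. A reader might infer from the 70–71% figures that the trial is underpowered, but those figures arise only under an unadjusted or change-score test, which is not the planned model.

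A reader might also object that 81 cases cannot detect a smaller *d* (0.60) than 89 cases (0.65). The text does not support that as a contradiction in itself: 0.65 is worded as an assumed, clinically based target, whereas 0.57 and 0.60 are given as minimum detectable values. What remains is that the text attaches 80% to 0.65.

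For WMHv, the defence is that a standardized difference can apply to any continuous outcome: if *d* is in SDs of change, 0.65 gives about 81% for WMHv too. That is right as arithmetic, but the paragraph gives no reason to expect 0.65 for WMHv. Equally, a reader might infer that WMHv power is low. The document does not show that either: on the baseline-SD scale, a high pre-post correlation would make the trial more sensitive.

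Two smaller discrepancies carry no weight. H1a splits the 89 cases 60/29 and H3 splits them 59/30, but this is rounding (72 × 0.82 = 59.0; 36 × 0.82 = 29.5) and moves the ANCOVA detectable *d* only from 0.555 to 0.550. The abstract claims power only "to detect changes in aerobic fitness", which is condensation and not a contradiction.

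**Conclusion.** The point holds in a limited form. For the same 89 cases, *r* and α, 80% power is attached to both 0.65 and 0.57, and one method cannot give both. Under the planned analysis, taken as two-sided with *r* = 0.50, the power at 0.65 is about 91%, an understatement of about 11 percentage points, and the other two claims stand at 82–83%. The sample size of 108 is not called into question for VO2peak.

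The 80% claim for WMHv is unsupported because its stated inputs are those of VO2peak. It is not shown to be false, and any WMHv magnitude depends on an assumed correlation.

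**What to change.** State the sidedness of α and use one method for all H1 figures. With two-sided ANCOVA, *r* = 0.50 and α = 0.05, report a detectable *d* of about 0.55–0.56 at 6 months (0.550 for 59/30, 0.555 for 60/29) and 0.58 at 12 months, with about 91% power at *d* = 0.65. Say that these are before any Holm adjustment. For scale, if the two primary outcomes were tested by Holm with a first step at 0.025 (an assumption, since the article does not fix the steps), the detectable values would be about 0.61 and 0.64.

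Take WMHv out of the VO2peak power sentence. Then either give it a detectable difference on its own analysis scale over a stated range of pre-post *r*, or state that it was not separately powered. If the first, treat the time points separately: about 0.64 × √(1 − *r*²) SD at 6 months and 0.67 × √(1 − *r*²) SD at 12 months.

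The cost is restated figures only, with no change to sample size, design or analysis.

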### Criteria for discontinuing or modifying allocated interventions {11b}

After 3 months of MICT, aerobic fitness non-response is determined in a three-hierarchical order as (1) < 5% increase in VO_2peak_ if peak cycle-ergometer exercise test with indirect calorimetry is completed at sufficient effort (e.g., respiratory exchange ratio ≥ 1.0 or HR ≥ 85% of the age-predicted max HR). (2) If exercise test is refused (e.g., participant wishes not to wear testing mask), non-response is indicated by < 10% increase in peak aerobic power (peak watts/kg) on the exercise test. (3) For participants who do not complete the exercise test, non-response is indicated by < 36.5-m increase in the distance of shuttle walk test (SWT). Non-responders are re-randomized 1:1 to HIIT or CARE for 3 months, stratefied by baseline age and random permuted blocks of 3 and 6. Responders continue MICT for 3 more months.

HIIT. An evidence-based “Scandinavian-style” HIIT protocol is used [22, 23]. This protocol includes 40 min of HITT comprising 5 sets of 4-min high-intensity cycling followed by 4-min moderate-intensity cycling. After a 10-min warm-up, participants progress to moderate intensity before the first set of HIIT. High intensity is prescribed as 80–85% HRR or RPE 15–16 for the first 8 weeks and increased to 80–90% HRR or RPE 15–17 after week 8. Following the HITT session, a 10-min cool-down period is conducted.

CARE. CARE includes 20-min resistance exercise followed by 30-min cycling. Resistance exercises target six major muscle groups (chest press, shoulder press, squats, rows, leg press, calf raises), are performed on exercise machines, and are adapted for any mobility or musculoskeletal issues reported by participants. Intensity is based on estimated one-repetition maximal strength (1RM) and progress following guidelines for older adults [24]. It starts with 2 sets of 10–12 repetitions at moderate intensity (50–60% 1RM, 9–11 RPE) and progressively increases to 70–85% 1RM or 13–16 RPE by week 7. Rest intervals are 1–2 min between sets. Cycling intensity is 65–75% HRR or RPE 12–14, like exercise prescription used during the MICT.

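### H2a and H2b assume HIIT–CARE effects that differ about six- to eightfold, and H2b's 80% power does not match its own example

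*Protocol article*

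**What the plan says.** All the figures are in the protocol article, Sample size {14}.

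- **H2a** (ordering of four group means on VO2peak) is planned on "small MICT + HIIT vs. MICT + CARE and MICT + HIIT vs. MICT differences", with d = 0.25–0.35, together with "moderate MICT only vs. stretching differences (*d*s = 0.40–0.55").
- **H2b** (non-responder or responder at month 6, in the re-randomised arms) is planned as follows: "assuming *n* = 13 per group, logistic-regression models are 80% powered to detect large between-group" differences. The example given is "≤ 2 non-responders in MICT + HIIT vs. ≥ 11 non-responders in MICT + CARE", at α = 0.05.
- The VO2peak scale is SD 4.8 mL/kg/min with a pre-post correlation of 0.50. A difference of 3.12 mL/kg/min is called clinically meaningful.

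Under Criteria for discontinuing or modifying allocated interventions {11b}, the main definition of non-response at month 3 is "< 5% increase in VO_2peak_ if peak cycle-ergometer exercise test with indirect calorimetry is completed at sufficient effort". Only these non-responders are re-randomised. Statistical methods {20a} analyses H2b by logistic regression on the second randomisation, adjusting for month-3 VO2peak.

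**The concern.** H2a and H2b look at the same two arms at the same visit, and VO2peak underlies both: as a mean in H2a, and cut at a threshold in H2b. The HIIT–CARE effect assumed for one should therefore be compatible with the effect assumed for the other. In consecutive sentences, one effect is called small and the other large, and nothing links them.

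H2b is the analysis confined to the two re-randomised arms. If the H2a effect is what the investigators expect, H2b has little chance of detecting it. A non-significant result could then be read as showing that HIIT is no better than CARE, when the trial could not have shown otherwise. A reader who sees 80% power beside H2b would have no warning of this.

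**Working it through.** **Inputs from the document:** 13 per arm; non-response 2/13 = 15.4% and 11/13 = 84.6%; α = 0.05 (two-sided assumed, since sidedness is not stated); d = 0.25–0.35; SD 4.8; baseline-to-follow-up r = 0.50, so the SD of change is 4.8 × √(2 × (1 − 0.50)) = 4.8; 5% rule.

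**Inputs that the document does not give (assumed):** mean baseline VO2peak, the month-3-to-6 correlation, and whether month-6 response is counted from baseline or from month 3.

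**1. The plan's own figure.** Summing the binomial probabilities of all 14 × 14 tables for 2/13 against 11/13 gives:

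| Test | Power |
|---|---|
| Chi-square or likelihood ratio | 98.8% |
| Fisher | 96.3% |
| Exact Wald (tables with a zero cell counted as non-significant) | 74.9% |
| Asymptotic Wald | 88.0% |

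The asymptotic Wald figure is Φ(2 ln(11/2) / √(2 × (1/2 + 1/11)) − 1.96) = Φ(3.409/1.087 − 1.96) = Φ(1.176). None of the four is 80%.

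**2. Size of the example.** Φ⁻¹(11/13) − Φ⁻¹(2/13) = 1.020 + 1.020 = 2.04 SD. Against the H2a effect: 2.04/0.35 = 5.8 and 2.04/0.25 = 8.2. In units, 2.04 × 4.8 = 9.8 mL/kg/min, against 0.25 × 4.8 = 1.2 to 0.35 × 4.8 = 1.7.

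**3. What 80% power requires.** With symmetric rates, 25% against 75% gives 82% power by chi-square (gap 1.35 SD), and 22% against 78% gives 80% by Fisher (gap 1.54 SD). Dividing by the H2a effect, 1.35/0.35 = 3.9 and 1.54/0.25 = 6.2. With HIIT held at 2/13, CARE non-response of about 64% (chi-square) or 71% (Fisher) is enough.

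**4. H2b power at the H2a effect, direct.** The HIIT rate is set to Φ(Φ⁻¹(CARE rate) − d).

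- CARE 60%: HIIT is 50.1% (d = 0.25) or 46.2% (d = 0.35). Power is 4.9% or 7.1% (Fisher), and 11.1% or 14.8% (chi-square).
- CARE 85%: HIIT is 78.4% or 75.4%. Power is 2.1% or 3.3% (Fisher), and 5.8% or 8.1% (chi-square).
- Over CARE rates of 30–85%: 2–7% (Fisher) and 6–15% (chi-square). At a CARE rate of 90%, Fisher falls to 1–2%.

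By the two-proportion formula, 80% power at this effect would need about 200–540 per arm.

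**5. The same, in selected month-3 non-responders.** I simulated baseline, month 3 and month 6 as trivariate normal, with SD 4.8, correlations with baseline of 0.50, assumed baseline mean 15–25, mean gain 0–3.12 and month-3-to-6 correlation 0.50–0.95. CARE adds nothing after month 3, and HIIT adds 1.2–1.68 mL/kg/min. With response counted from baseline, power is 3–15% (Fisher), 8–27% (chi-square), 9–29% (likelihood ratio) and 1–12% (exact Wald).

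If response is instead counted from month 3, power stays at or below 20% for month-3-to-6 correlations up to 0.70. It rises to at most 66% (likelihood ratio) at 0.95.

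**The case against.** The section calls the H2b effect large and offers the counts only as an example, so this can be read as a statement of what is detectable and not as a prediction. That is fair, but it does not tell the reader that the detectable difference is several times the one assumed in the sentence before.

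H2a is a four-group ordering test whose power also comes from the larger MICT–stretching difference, and comparing d with two proportions needs a latent normal model that the document does not state. Both points stand as caveats. They explain why H2a can have power, but they do not make the two HIIT–CARE effects agree.

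The 80% might come from an asymptotic Wald calculation with an allowance for the covariate: an R² of 0.20 gives 80.1%. The document states no such allowance.

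Three stronger readings are tempting, and the document does not support them:

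- **That 80% power needs a 2 SD gap or 85% non-response under CARE.** Steps 1 and 3 show that it does not.
- **That 85% non-response under CARE cannot be reached with the plan's SD, correlation and 5% rule.** If r = 0.50 also held between months 3 and 6 and CARE added nothing, 55–74% would remain non-responders from baseline. But the document gives 0.50 only as a pre-post correlation. At a month-3-to-6 correlation of 0.85 the range is 76–86%, at 0.90 it is 80–89%, and at 0.95 it is 86–92%.
- **That a fixed share, such as 40%, would convert through regression to the mean alone.** On the same assumptions, conversion from baseline runs from about 8% (100 − 92) to 45% (100 − 55). H2b is in any case a between-arm comparison.

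**Conclusion.** The point holds as an unreconciled pair of planning assumptions plus a power figure that does not fit its own example. The 2.04 SD gap and the mismatch with 80% follow from the stated counts, given a two-sided α and, for the gap, a latent normal scale.

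The stated 80% is too low for its example under Fisher, chi-square, likelihood-ratio and asymptotic Wald tests, and too high only under exact Wald. The more serious matter is that, at the effect planned for H2a, H2b power is about 1–29% when response is counted from baseline. That range depends on the test, the non-response rate and the assumed baseline mean and month-3-to-6 correlation, and it leaves out any gain or loss from adjusting for month-3 VO2peak. Counting response from month 3 can raise power when the two visits correlate very highly, but no setting tried reached 80%.

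The document does not support a claim that the H2b example is impossible.

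**What to change.** In Sample size {14}:

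1. Base H2a and H2b on one HIIT–CARE effect, or state plainly that H2b can detect only differences far larger than those planned for H2a.
2. Correct the pairing of 80% with 2 against 11 non-responders: name the test, and any covariate allowance, and give the power or the rates that go with it.
3. Restate H2b power at d = 0.25–0.35 as a range. Give the assumed CARE non-response rate, the month-3-to-6 correlation, and the visit from which month-6 response is counted.

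In Statistical methods {20a}, state that H2b will be reported as a HIIT–CARE difference with its confidence interval, so that a non-significant result is not read as HIIT being no better. Do not write a single regression-to-the-mean conversion rate into the protocol, because the inputs for it are not given.

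The cost is wording and a less favourable power statement for H2b. Neither the design nor the number of patients changes.
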